### Quantitative Component

#### Sexual Function

The FSFI is a validated 19-item instrument that assesses 6 domains of sexual function: desire, arousal, lubrication, orgasm, satisfaction, and pain. Each domain generates an individual score, and the total FSFI score is the sum of all domain scores, with a maximum of 36 points. A total score below 26.55 indicates sexual dysfunction. Authorization for the use of the FSFI has been obtained [22].

#### Health-Related Quality of Life

The EORTC QLQ-C30 version 3.0 is a validated 30-item instrument designed to assess health-related quality of life across 3 scales: functional, global quality of life, and symptoms. The functional and global scales range from 0 to 100, with higher scores indicating better functioning or overall quality of life. The symptom scale (eg, fatigue, pain, and insomnia) also ranges from 0 to 100, where lower scores reflect fewer symptoms and, therefore, better quality of life. Authorization for the use of the EORTC QLQ-C30 has been obtained [23].

### Qualitative Component

Qualitative insights on barriers, facilitators, and perceptions of sexual health and well-being will be derived from focus groups, semistructured interviews, participant observation field notes, and anonymous postsession diaries.

### Sociodemographic and Clinical Characteristics

At session 1 (before the intervention), participants will complete a brief self-administered questionnaire capturing age, educational level, employment status, relationship status, parity, menopausal status, time since diagnosis and completion of primary treatment, cancer type and stage (self-reported), prior and current treatments (including topical vaginal estrogen), relevant comorbidities and medications, pelvic floor therapy history, and sexual activity and partner status. Sensitive items are optional and include a “prefer not to answer” choice.

Participants will complete the sociodemographic questionnaire and baseline FSFI and EORTC QLQ-C30 at session 1 and repeat the FSFI and EORTC QLQ-C30 at session 3. Focus groups and semistructured interviews will be audio recorded and transcribed verbatim; participant observation field notes and anonymous diaries will be collected after each session. Optional one-to-one counseling is not recorded; clinicians may keep brief field notes. Trained staff will enter data into REDCap (Research Electronic Data Capture; Vanderbilt University).

Before each in-person session, participants receive a telephone call inviting them to attend the session. During the call, transportation needs are assessed; if necessary, transportation is arranged by the research team. Participants are informed that meals and refreshments are provided free of charge. If desired, participants may bring an accompanying adult family member who may attend the group sessions but will not participate in interviews or individual counseling to maintain privacy and confidentiality. To uphold participants’ autonomy and freedom, all individuals are explicitly informed that voluntary withdrawal is allowed at any time without penalty. This ensures full participant control over involvement and minimizes the risk of perceived coercion.

Personal, religious, or moral values will not be imposed. No judgments about patients’ sexual lives that could generate stigma, guilt, or shame are permitted. Inappropriate or nonconsensual language or materials are prohibited. Explicit or mocking sexual content is prohibited unless educationally justified and previously consented to by participants. Private information will not be disclosed without authorization. It will be strictly forbidden to deny or ignore the needs of lesbian, gay, bisexual, transgender, and queer survivors. Heteronormative assumptions are not permitted; all content must be inclusive and adapted to participants with nonbinary identities or same-sex partners. Unqualified or clinically unsupported interventions will not be allowed. All professionals must present credentials accrediting their expertise and complete training in cultural sensitivity and sexual ethics to prevent stigma and bias.

### Sample Size

The quantitative pretest-posttest sample size was calculated based on mean differences and an adjusted SD of 0.69, informed by prior studies such as Starting the Conversation, a pilot trial using the FSFI to assess sexual function in survivors of gynecological cancer [11]. Assuming a moderate effect size (*d*=0.5), a 95% confidence level, and 80% power, the estimated sample size is 60 participants. Calculations were performed using G*Power (Heinrich Heine University Düsseldorf), a standard tool for sample size estimation in mean difference studies.

For the qualitative strand, sample adequacy is guided by the information power principle—considering study aim, sample specificity, quality of dialogue, and analytic strategy—rather than numeric saturation targets [24]. We purposefully seek heterogeneity in survivorship stage and symptom profiles to capture a range of experiences relevant to sexual health education.

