## Methods

### Design

This is a prospective, single-center, single-group (pretest-posttest) mixed methods feasibility study designed to evaluate the implementation and acceptability of an educational psychosexual intervention for survivors of gynecological cancer. Estimating preliminary effectiveness is a secondary objective. This is not a definitive effectiveness trial but an initial step to determine whether the intervention can be delivered successfully and is acceptable to participants.

This study uses an embedded convergent mixed methods design, giving equal priority to quantitative and qualitative strands. Quantitative data (FSFI and EORTC QLQ-C30 scores) will be collected at baseline (before session 1) and after the intervention (end of session 3). Qualitative data (focus groups, semistructured interviews, participant observation field notes, and anonymous diaries) will be gathered after each session. Integration will occur during interpretation through meta-inferences and joint displays that juxtapose pretest-posttest quantitative changes with qualitative themes related to sexual well-being, communication, agency, and body image. We will seek convergence, complementarity, and expansion; discrepancies will be examined to refine inferences and inform practical recommendations.

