### Analysis Plan

#### Quantitative Analysis

Continuous variables will be summarized as means with SDs or medians with IQRs depending on the distribution, assessed using the Shapiro-Wilk test. Categorical variables will be presented as absolute and relative frequencies. Primary analyses will evaluate within-group changes (session 1 vs session 3) in FSFI and EORTC QLQ-C30 scores. For continuous outcomes, paired 2-tailed *t* tests will be used when normality assumptions are met; otherwise, Wilcoxon signed rank tests will be applied. A 2-sided significance level of α=.05 will be adopted. Effect sizes will be reported (Cohen *dz* for paired *t* tests; *r* for the Wilcoxon signed rank test), along with 95% CIs and graphical representations of response distributions. Missing data will be described; if they constitute >5% and are plausibly missing at random, an exploratory sensitivity analysis using multiple imputation will be performed.

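### The sample size of 60 at 80% power does not follow from its stated inputs: for a paired t test with dz=0.5, 34 pairs suffice and 60 give about 97% power

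*Protocol article*

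**What the plan says.** The Design section describes a "prospective, single-center, single-group (pretest-posttest) mixed methods feasibility study". The Sample Size section opens with "The quantitative pretest-posttest sample size was calculated based on mean differences and an adjusted SD of 0.69", an SD that it says was informed by prior studies, including a pilot trial that used the FSFI. It then fixes a moderate standardised effect, d=0.5, and concludes with "a 95% confidence level, and 80% power, the estimated sample size is 60 participants". The calculation is attributed to G*Power. The section gives no attrition allowance, pre-post correlation or multiplicity adjustment.

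The Quantitative Analysis section compares session 1 with session 3 by paired t tests, or by Wilcoxon signed rank tests if normality fails. It adds "A 2-sided significance level of α=.05 will be adopted" and names the effect size to be reported as "Cohen *dz* for paired *t* tests". The Measures and Outcomes section sets a retention threshold of at least 80%. The Prespecified Study Aims make feasibility and acceptability primary, and within-group change in FSFI and EORTC QLQ-C30 secondary.

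**The concern.** A paired design needs far fewer participants than 60 to detect half a standard deviation of change with 80% power. The article prints both the inputs and the result, and they disagree. This is therefore not a detail left to a fuller protocol or an analysis plan.

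The paragraph also mixes two kinds of input. A standardised effect already contains the SD, so a calculation that assumes d=0.5 cannot also depend on an SD of 0.69. The text does not say whether 0.69 is the SD of single scores or of changes, what scale it is on, or what was adjusted.

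This paragraph is the only numerical support for the enrolment target. As written, it does not tell a reader what change the study can detect. It matters in practice too: the Results section reports 13 women enrolled by July 2025, with recruitment planned to end in September 2025. Whoever judges the final number will hold it against 60.

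**Working it through.** **Inputs.** One group measured twice (Design); d=0.5, 95% confidence, 80% power, SD 0.69, N=60 (Sample Size); two-sided .05, paired t test, dz reported (Quantitative Analysis); retention of at least 80% (Measures and Outcomes).

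**1. Attempt to reproduce 60.** The normal approximation for a paired comparison is n = ((z for α/2 + z for power)/dz)² = ((1.960 + 0.842)/0.5)² = 31.4, so 32. The exact calculation uses the noncentral t distribution with n−1 degrees of freedom and noncentrality dz·√n:
- n=33: power 79.5%
- n=34: power 80.8%, the smallest n that reaches 80%
- n=48: power 92.4%
- n=60: power 96.8%

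The stated figure is not reproduced. At 80% power, 60 pairs detect dz = 0.37.

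**2. Other paired settings with dz=0.5.**

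| Setting | n |
|---|---|
| One-sided .05, 80% power | 27 |
| Two-sided .05, 90% power | 44 |
| Two-sided .05, 95% power | 54 |
| Two-sided .01, 80% power | 51 |
| Wilcoxon, efficiency 0.955 (34/0.955) | 36 |
| Wilcoxon, worst-case efficiency 0.864 (34/0.864) | 40 |
| Bonferroni for 10 comparisons | 58 |
| Bonferroni for 15 comparisons | 62 |

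A correction for a number of comparisons between the last two rows would land near 60. The article states an unadjusted .05, however, so this is not a reading of its inputs.

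**3. Attrition.** Getting from 34 to 60 needs a loss of 1 − 34/60 = 43%. At 80% retention the inflation is 34/0.8 = 42.5, so 43 enrolled.

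**4. d scaled to the SD of single scores.** Here dz = d/√(2(1−ρ)), where ρ is the pre-post correlation. No value is stated, so the range is shown:

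| ρ | n |
|---|---|
| 0 | 65 |
| 0.1 | 59 |
| 0.3 | 46 |
| 0.5 | 34 |
| 0.7 | 21 |

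Setting dz to 0.3677, the effect detectable with 60 pairs, gives ρ = 1 − (0.5/0.3677)²/2 = 0.08. An n of exactly 60 corresponds to ρ of about 0.08 to 0.09.

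**5. 0.5 as a raw difference, 0.69 as the SD of change.** dz = 0.5/0.69 = 0.725, and n = 17.

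**The case against.** **The figure of 34 is conditional.** The Sample Size section writes d, not dz; dz appears only as the effect size to be reported. If d refers to single-score SDs, the requirement depends on a correlation that the article does not give, and 34 then holds only at ρ=0.5. This stands, and 34 should not be presented as the one proven requirement. It does not rescue 60, because a correlation of about 0.08 to 0.09 is implausibly low for the same questionnaire repeated in the same women over about three weeks.

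**An attrition allowance may sit in the full protocol.** It may, but it would have to be about 43%, which fits poorly with a retention threshold of at least 80%. That threshold is itself a feasibility success criterion, not a stated planning assumption.

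**The error is harmless in direction and peripheral in purpose.** This largely stands. On the dz reading, 60 is more than enough, and the article says plainly that it is not a definitive effectiveness trial. The concern that the figure will be carried into the later comparative study is speculative: the article says that the study's results will guide that design, not this sample size.

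**A two-group formula as the source.** A reader might infer that 60 is a two-arm total, since 2 × ((1.960 + 0.842) × 0.69/0.5)² = 29.9, or 30 per group. The documents do not support this. No second group is mentioned, 0.5 is called a standardised effect, and the exact t calculation gives 31 per group, 62 in total.

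**Conclusion.** The point holds in a limited form. For the single-group paired design, N=60 at 80% power does not follow from the stated inputs. With d read as dz, two-sided .05 and 80% power, the requirement is 34 pairs; 60 pairs give about 97% power and 48 completers about 92%. The SD of 0.69 is undefined, and redundant once d is fixed.

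A reader might also infer that the study targets a change of 0.5 × 0.69 = 0.345 points on an instrument of which the article says "the total FSFI score is the sum of all domain scores, with a maximum of 36 points". That follows only if 0.69 is the SD of change in FSFI total points, which is not stated.

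Nor do the figures show an underpowered or invalid analysis. Power is understated, no shortfall arises if 60 is reached, and the comparison serves a secondary aim. This is a should-fix.

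**What to change.** Rewrite the Sample Size paragraph so that it:
- names the paired t test at two-sided .05;
- defines the effect size, either as dz or as d with the assumed pre-post correlation;
- states any attrition allowance;
- gives figures that match. If dz=0.5 is meant: 34 evaluable pairs give 80% power; 60 enrolled with 48 evaluable give about 92%; 60 evaluable pairs detect dz of about 0.37 at 80% power;
- deletes the 0.69, or states its units, what was adjusted, and whether it is the SD of the paired change.

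If 60 is kept, justify it by the precision of the primary feasibility proportions. Around 80%, the 95% half-width with 60 women is 1.96 × √(0.8 × 0.2/60) = 0.101, about ±10 points. That serves the primary aim better than a power calculation on a secondary outcome.

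The cost is one paragraph of wording and no extra participants.

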### Measures and Outcomes

The primary objective is feasibility and acceptability. We will quantify feasibility (eligibility, invitation, consent, recruitment rate, retention, attendance and adherence, fidelity, and data completeness) and acceptability (postsession satisfaction, perceived usefulness, and comfort; recommendation item scored from 0‐10). A priori thresholds are as follows: retention of ≥80%, attendance of ≥80% per session, fidelity of ≥80%, data completeness of ≥85%, no serious adverse events, acceptability mean of ≥4.0/5, and net promoter score of ≥30.

As a secondary objective, this study assesses quantitative outcomes using validated psychometric tools and qualitative dimensions using reflexive thematic analysis. Mixed methods integration will offer a comprehensive understanding of EDUSEXONCO’s effects on sexual rehabilitation and psychosocial recovery.

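### The planned 60 participants do not follow from the stated inputs: with d=0.5 read as Cohen dz, the planned paired test needs 34 pairs for 80% power, and 60 pairs give 96.8%

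*Protocol article*

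**What the plan says.** The Sample Size section of the protocol article sizes the quantitative pretest-posttest comparison. The size was "calculated based on mean differences and an adjusted SD of 0.69", informed by an earlier pilot trial that used the FSFI. It continues "Assuming a moderate effect size (*d*=0.5"), and with "a 95% confidence level, and 80% power, the estimated sample size is 60 participants". G*Power is named as the software. The section gives no pre-post correlation, second group, multiplicity adjustment or loss allowance.

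The Design section describes a "single-group (pretest-posttest) mixed methods feasibility study". Under Quantitative Analysis, "paired 2-tailed *t* tests will be used when normality assumptions are met; otherwise, Wilcoxon signed rank tests will be applied", and "A 2-sided significance level of α=.05 will be adopted". The same section names Cohen dz as the effect size to be reported with the paired t test.

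**The concern.** An effect size, a significance level, a power and a test together fix the sample size. All four can be read from the article, and 60 is well above what a paired test at d=0.5 usually needs. Either the size was computed for another test, or 0.5 does not mean what its label says, or a further assumption was used and not reported.

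What is at stake is whether the power statement can be relied on. Sixty is the only enrolment figure in the article. The Results section reports 13 women enrolled by July 2025, with recruitment planned until September 2025. A reader who sees fewer than 60 at the end could conclude that the planned power was lost, when on the dz reading 34 pairs would provide it. The article also says that this study will guide a later comparative multisite study, which could take over an effect, size and power that do not fit together.

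**Working it through.** **Inputs.** One group, measured before and after (Design). Paired two-tailed t test at two-sided α=0.05, with dz as effect size (Quantitative Analysis). d=0.5, 80% power, SD 0.69 and stated result 60 (Sample Size). Retention threshold of at least 80% (Measures and Outcomes).

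**1. The plan's figure under the plan's test.** Reading d as dz, power comes from the noncentral t distribution with n−1 degrees of freedom and noncentrality dz·√n:

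| Pairs | Power at dz=0.5 |
|---|---|
| 33 | 79.5% |
| 34 | 80.8% |
| 48 (80% of 60) | 92.4% |
| 60 | 96.8% |

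The required number is 34. The normal approximation agrees closely: ((1.96+0.8416)/0.5)² = 31.4, so 32. The stated 60 is not reproduced. At 80% power, 60 pairs detect dz of about 0.37 and 48 pairs about 0.41.

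**2. Variants of the same test.** None reaches 60:
- One-sided: 27.
- Wilcoxon signed rank, dividing by its relative efficiency: 34/0.955 gives 36; the worst case 34/0.864 gives 40.
- 20% loss, matching the retention threshold: 34/0.8 = 42.5, so 43. With the Wilcoxon figures as well: 45 to 50.
- 90% power: 44. 95% power: 54.

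Reaching 60 from 34 by loss alone would need 1−34/60 = 43% dropout.

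**3. The inputs against each other.** If 0.69 is the SD that standardises the effect, d=0.5 is a raw difference of 0.5×0.69 = 0.345. If 0.5 is a raw difference, the standardised effect is 0.5/0.69 = 0.72, and a paired test with 0.69 as the SD of the differences needs only 17 women. Neither reading gives 60 under a paired test: 17 for the second, 34 for the first.

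**4. Routes that do come near 60.**
- *Two independent groups, normal formula, 0.5 as a raw difference:* 2×(1.96+0.8416)²×0.69²/0.5² = 29.9, so 30 per group and 60 in total. The exact t calculation gives 31 per group, 62 in total; 30 per group has 78.8% power. With standardised d=0.5, two groups would need 64 each, 128 in total.
- *d on the raw-score SD, with pre-post correlation ρ:* dz = 0.5/√(2(1−ρ)). The required number is 65 at ρ=0, 61 at ρ=0.07, 59 at ρ=0.1, 46 at ρ=0.3 and 34 at ρ=0.5. So 60 would correspond to a correlation of a little under 0.1.

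The article states neither a second group nor a correlation.

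**The case against.** The strongest objection is that 34 is conditional. The Sample Size section says d, and only the analysis section says dz. If d is scaled by the SD of the raw scores, the required number depends on a correlation that the article does not give, and a value near 0.1 would produce about 60. This stands as a limit on the claim. Such a correlation seems low for one questionnaire repeated over about three weeks, but nothing in the article settles it. The dz reading is the natural one because dz is the measure that the analysis names, and it has to be stated as an assumption.

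A reader might infer from the exact match at 30 per group that a two-group formula was used by mistake. The article does not support that as a finding. The match needs the normal approximation, whereas the article names G*Power, whose exact t calculation gives 62. It also needs 0.5 to be a raw difference, although the article labels it d. It is one possible source and no more.

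A reader might also infer that the trial is being judged against a wrong recruitment target, or that the lack of a loss allowance weakens it. The a priori thresholds, such as "retention of ≥80%, attendance of ≥80% per session", set no target of 60. With 80% retention, 48 pairs still have 92.4% power on the dz reading, so the absent allowance does no harm there.

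Finally, the error is on the safe side, the paired tests serve a secondary aim, and the article disclaims definitive effectiveness estimates. A feasibility study may also want more than 34 women for reasons unrelated to this test. All of that stands, and it lowers the severity. It does not make the power statement correct: the mismatch lies in figures that the article prints, not in detail left to a fuller document.

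**Conclusion.** The point holds. For a single-group paired two-sided 5% t test with d read as dz, the stated inputs give 34 pairs, not 60, and 60 pairs have 96.8% power, not 80%. Separately, d=0.5 and SD 0.69 imply a raw difference of 0.345; if 0.5 was itself the raw difference, the effect is 0.72 and the label d is wrong. How 60 was obtained cannot be established from the article.

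The conclusion rests on d meaning dz. On the raw-score SD the required number runs from 65 at zero correlation to 34 at a correlation of 0.5, and an unreported correlation would then have to be given.

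This should be fixed, but it is not critical. The planned size exceeds what the paired test needs on the dz reading, and no conclusion on the primary feasibility and acceptability objective changes. It does not follow that the trial is too large or that enrolment should be cut.

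**What to change.** Rewrite the Sample Size paragraph for the paired test. If 0.5 is meant as dz, wording such as this would do: *Thirty-four women with paired scores give 80% power (two-sided 5%) for dz=0.5. The planned 60 give 97% power for dz=0.5 if all have paired scores, or 92% with 48 pairs at 80% retention; the effects detectable with about 80% power are dz=0.37 and dz=0.41 respectively.*

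In the same paragraph, state:
- the G*Power test family that was used;
- whether 0.5 is a raw or a standardised difference and, if it is scaled by the raw-score SD, the pre-post correlation assumed;
- what the SD of 0.69 refers to and how it was adjusted;
- if 60 is kept, its actual justification, for example the precision wanted for the feasibility measures, if that was the reason.

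The cost is one paragraph. No extra patients and no change to design or analysis are needed.

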### Analysis Plan

#### Quantitative Analysis

Continuous variables will be summarized as means with SDs or medians with IQRs depending on the distribution, assessed using the Shapiro-Wilk test. Categorical variables will be presented as absolute and relative frequencies. Primary analyses will evaluate within-group changes (session 1 vs session 3) in FSFI and EORTC QLQ-C30 scores. For continuous outcomes, paired 2-tailed *t* tests will be used when normality assumptions are met; otherwise, Wilcoxon signed rank tests will be applied. A 2-sided significance level of α=.05 will be adopted. Effect sizes will be reported (Cohen *dz* for paired *t* tests; *r* for the Wilcoxon signed rank test), along with 95% CIs and graphical representations of response distributions. Missing data will be described; if they constitute >5% and are plausibly missing at random, an exploratory sensitivity analysis using multiple imputation will be performed.

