EDUSEXONCO is delivered as a sequence of 3 progressive theoretical-practical workshop levels (basic, intermediate, and advanced) to support gradual learning and skill acquisition. Each level includes two complementary strands: (1) a medical-sexual strand focused on anatomy and sexual response, treatment-related sexual changes, symptom self-management (eg, lubrication, pain, and dyspareunia), and safe use of supportive resources; and (2) a sociopsychological strand focused on stigma reduction, communication, consent and boundaries, self-compassion and body image, emotional regulation, and social reintegration. Each workshop incorporates brief guided practice (eg, “anatomy tour” using 3D models, communication scripts, sensate focus–inspired exercises, paced breathing, pelvic floor downtraining, and gentle yoga and relaxation), a take-home task to reinforce learning between sessions, and fidelity markers (eg, coverage of key items, completion of role-plays or practice, and delivery of handouts) to standardize delivery across facilitators. The full-day schedule is provided in Multimedia Appendix 2. A detailed topic-by-level syllabus including objectives, key content, practices, materials, leads, take-home tasks, fidelity markers, and qualitative prompts is provided in Multimedia Appendix 3. Examples of the semistructured interview guide are provided in Multimedia Appendix 4.

In-person group delivery takes place in education or rehabilitation rooms with acoustic privacy at FVL comprising 3 sequential full-day sessions (approximately 8 hours each) over approximately 3 weeks (roughly 24 hours in total). The intervention includes optional home practice for 10 to 15 minutes per day.

Language and examples are culturally adapted to Colombia, alternatives are provided for participants without a partner, activities are adapted for pain or mobility limitations, and Spanish-language materials target approximately B1 to B2 readability.

Fidelity is monitored using per-session checklists covering objectives, core activities, materials, timing, inclusivity, skill practice, and end-of-session outputs (anonymous diaries). Attendance and adherence logs capture session-level participation (sessions 1‐3), completion of pretest and posttest questionnaires, participation in the group interview and optional 1:1 counseling, and take-home practice reporting.

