#### Pretrial Piloting and Feasibility Testing

Core components were piloted with a convenience sample of eligible survivors (n=15) to assess feasibility (recruitment and retention, session length, and logistics), acceptability (satisfaction, perceived usefulness, and comfort discussing sexual health), and fidelity (adherence to the manual). During pretrial piloting, full-day sessions were identified as a potential feasibility barrier; consequently, contingency adaptations (shorter session blocks, optional hybrid delivery, and flexible scheduling) were prepared while preserving the protocol’s objectives and core content. In this study, brief participant and facilitator feedback will be reviewed after each session to inform minor, prespecified logistical refinements (eg, scheduling and session length and pace) for subsequent groups without modifying core content or learning objectives. These findings guided the final structure of the sessions and the implementation plan to be used.

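### Paired tests treat women taught in the same workshop group as independent; if their changes correlate, the intervals for FSFI and QLQ-C30 change are too narrow

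*Protocol article*

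**What the plan says.** The Quantitative Analysis section sets the contrast: "Primary analyses will evaluate within-group changes (session 1 vs session 3) in FSFI and EORTC QLQ-C30 scores". Here within-group refers to the single study cohort, not to a workshop group. The next sentence fixes the methods. Paired t "tests will be used when normality assumptions are met; otherwise, Wilcoxon signed rank tests will be applied". It adds "A 2-sided significance level of α=.05 will be adopted", and effect sizes are to be reported "along with 95% CIs and graphical representations of response distributions". No term for workshop group, cluster-robust error or ICC is mentioned, and the Sample Size section has no design effect.

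Delivery is collective. The Intervention section says "In-person group delivery takes place in education or rehabilitation rooms with acoustic privacy at FVL", over three full-day sessions totalling roughly 24 hours, with large-group workshops and individual counseling only as an option. The Pretrial Piloting and Feasibility Testing section shows that more than one group is planned: after feedback, minor prespecified logistical changes, such as to scheduling or session length and pace, may be made "for subsequent groups without modifying core content or learning objectives". The same section and the Results section hold shorter blocks and hybrid delivery in reserve.

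The only group size given, 6 to 8, is for the group interviews. The number and size of the workshop groups are not stated.

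**The concern.** The paired t test and the signed rank test remove variation between women at baseline. They still require that one woman's change tells nothing about another's. Women who spend three full days together share peers, dates, session format and whatever happened in the room. The Comparison With Prior Work section names peer learning and validation as a particular value of group formats, and that mechanism could make changes within a group resemble one another. Planned adjustment of logistics between groups adds another possible source of difference.

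If such correlation exists, the standard error of the mean change is understated, the nominal 95% CI covers less than 95%, and P values are too small. The mean change itself is not affected. Because the protocol names the tests, this is a stated method whose assumption sits badly with the stated delivery, not a detail left for a later document.

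**Working it through.** **Inputs from the protocol.** Two-sided alpha 0.05 and paired tests with 95% CIs (Quantitative Analysis); N = 60, d = 0.5, 80% power (Sample Size).

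**Inputs assumed, because the protocol gives none.** ICC of the change score from 0 to 0.10; layouts of 8 groups of 7 (56 women) and 4 groups of 15 (60 women).

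**The plan's own figure.** The sample size statement reads "a 95% confidence level, and 80% power, the estimated sample size is 60 participants". A paired t test with d = 0.5, two-sided 0.05 and 80% power needs 34 women by the noncentral t method (normal approximation: ((1.96 + 0.84)/0.5)² = 31.4, so 32). The stated 60 does not follow from these inputs. That is a separate matter. It matters here only because the gap cannot be read as a clustering allowance: none is stated.

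**Step 1, design effect.** For groups of size m, DE = 1 + (m − 1) × ICC. The standard error should be larger by √DE.

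- 8 groups of 7, ICC 0.05: DE = 1 + 6 × 0.05 = 1.30; √1.30 = 1.14; effective N = 56/1.30 = 43.
- 4 groups of 15, ICC 0.05: DE = 1 + 14 × 0.05 = 1.70; √1.70 = 1.30; effective N = 60/1.70 = 35.
- Groups of 8, ICC 0.01: DE = 1 + 7 × 0.01 = 1.07; √1.07 = 1.03, so about 3% more width.
- ICC 0: DE = 1; nothing changes.

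**Step 2, type I error of the plain paired t test.** Approximately P(|Z| > 1.96/√DE). For 8 groups of 7 at ICC 0.05, 1.96/1.14 = 1.72, giving about 8.6%. For 4 groups of 15, 1.96/1.304 = 1.50, giving about 13%. Simulation under no true change agrees:

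| Layout | ICC 0.01 | ICC 0.02 | ICC 0.05 | ICC 0.10 |
|---|---|---|---|---|
| 8 groups of 7 | 5.7% | 6.3% | 8.6% | 12.5% |
| 4 groups of 15 | 6.8% | 8.4% | 13.0% | 20.7% |

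A t test on the group means held close to 5% in the same simulations.

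**Step 3, cost of a group-level interval.** √DE alone understates the extra width, because degrees of freedom fall to the number of groups minus one. For a t interval on group means at ICC 0.05:

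- 8 groups of 7: (2.36/2.00) × 1.14 = 1.35 times the paired CI.
- 4 groups of 15: (3.18/2.00) × 1.30 = 2.07 times.
- 2 groups: 12.71/2.00 = 6.4 times from degrees of freedom alone, which is uninformative.

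At dz = 0.5, power of the group-mean test with 4 groups of 15 is about 53% at ICC 0.05 and 73% at ICC 0. The plain paired test at N = 60 and ICC 0 has 96.8%.

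**The case against.** The strongest reply is that nothing in the documents shows a positive ICC for change. A reader might infer that the intervals will be too narrow. The documents do not support that: they give no ICC, number of groups or group size, and with small groups and an ICC of 0.01 the effect is negligible. This part of the reply stands, and the point is conditional.

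A reader might also infer that groups differ because their facilitators differ. The protocol instead describes one multidisciplinary team at one center, a facilitator manual and fidelity checklists, with only minor prespecified logistical changes between groups. Facilitator differences are therefore not shown. Shared peers, dates and format remain plausible sources of correlation, of unknown size.

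Third, the stakes are modest. Change in FSFI and QLQ-C30 is a secondary aim, the a priori thresholds concern feasibility and acceptability, and the limitations section disclaims definitive effectiveness estimates. This stands too. However, the analysis section calls these analyses primary and attaches a significance level, and the Sample Size section sizes the study on them.

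Fourth, few groups make the remedy weak. Thirteen women had enrolled by July 2025, with recruitment planned to close in September, so two or three groups is a realistic outcome. The ICC would also be poorly estimated: with a true value of 0.05 and 4 to 8 groups, about 35% of simulated studies gave an estimate of zero or below, with a 95% sampling range of roughly −0.1 to 0.27. The protocol says the results will guide the next study, but not that a variance component from this one will. This limits what the fix can deliver; it does not make the independence assumption safe.

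**Conclusion.** The concern holds in conditional form. The protocol fixes tests that treat women as independent while describing delivery to successive groups. If changes correlate within groups, the 95% CIs are too narrow and type I error exceeds 5%. At an assumed ICC of 0.05 the error is about 8.6% (8 groups of 7) to 13% (4 of 15). The problem is close to nil at an ICC of 0.01 with small groups and absent at 0. All of these sizes rest on assumed ICCs and group layouts. The estimated mean changes stand; what is unsupported is the precision claimed for them. The consequence is limited by the secondary, preliminary status of the change scores, but the remedy is cheap enough to be worth making.

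**What to change.** State the number and size of workshop groups, and record each woman's group in REDCap; the attendance logs should already allow this. Report mean change by group, and the ICC of change with its uncertainty. Beside the paired-test CI, report a CI for the mean change from a model of change with a random intercept for workshop group and small-sample degrees of freedom. An ICC estimate of zero from few groups should not be read as evidence of independence.

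If there are too few groups for a useful group-level interval (about 2 to 4), keep the paired CI, show change by group, and state that the CI and P value assume independence between women taught together.

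The cost is one variable and a few lines in the plan. The real price is width: at ICC 0.05 a group-means interval is about 1.35 times as wide for 8 groups of 7 and about 2 times for 4 of 15, with the power loss shown above. That is why it should sit beside the paired interval and not simply replace it.
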